- ii. Effectiveness is defined as a 7-day biochemically verified point prevalence abstinence from combustible tobacco products at 6 months using CO Check+. Our sample size (n=750 participants) has sufficient power to show at least 8% increase in a clinical effectiveness endpoint in the implementation group relative to standard of care (SOC) in the control group.
- 2. To assess the Adoption and Implementation of BSMART indexed by quality and consistency of intervention delivery.
  - i. identify how BSMART can be tailored to the network of HIV clinics in Botswana for adoption and implementation fidelity,
  - ii. foster comparison across clinical sites, and
  - iii. inform the development of activity logs to track implementation strategies.
- 3. To assess whether the intervention becomes Maintained as part of routine practices over time across HIV care facilities.
  - i. determine the extent to which the core components of BSMART and implementation strategies continue to be delivered and are maintained over time with fidelity and
  - ii. using the Program Sustainability Assessment Tool (PSAT), determine how organizational capacity and infrastructure to deliver BSMART are maintained, including partnerships, networks, and coalitions.
- 4. To determine the preliminary cost-effectiveness of BSMART - the incremental net monetary benefit at 6 months of follow-up in order to compare the value of BSMART to standard of care (SOC).

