### **Hypothesis:**

The BSMART intervention (SBIRT and varenicline) will

- i. Increase the proportion of smokers able to quit smoking
- ii. Increase the number of attempts to quit smoking
- iii. Increase the length of abstinence in failed quit attempts
- iv. Decrease the number of cigarettes smoked every day
- v. Decrease the number of days of using combustible products within the past month
- vi. Decrease the number of days of using combustible products within the past three months in people exposed to the intervention as compared to people in the control phase

**Potential Impact:** Addressing the syndemic between tobacco use and HIV infection in a coordinated manner aligns with the NIH HIV/AIDS priorities for effective cancer control among PLWH in a high HIV prevalence setting. This study is significant because it integrates smoking cessation interventions, which are lacking in sub-Saharan Africa (SSA), into a real-world HIV care system that has been underpinned by a robust PEPFAR/CDC program and leverages long-standing partnerships with Ministry of Health and Wellness and the University of Botswana's Anti-tobacco Network for population, health system, and policy level impact.

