## Process and Outcome Measures

### 1. Clinical Outcomes

Primary Outcome: The clinical effectiveness endpoint at six months is the 7-day point prevalence abstinence from combustible tobacco products validated primarily by breath CO < 6 ppm. The failure for this measure is any smoking (even a puff) during a 7-day window.

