#### Secondary Outcomes:

- Quit attempts
- Length of successful quitting during each attempt
- Number of cigarettes currently smoked, and
- Number of days of using combustible tobacco products for at least 24 hours within the past month and the last 3 months.

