## Power and Sample size

Our sample size is based on the hypothesis that interventions will have a substantial impact on primary endpoints compared to the control phase (Figure 5).

**Main effect:** Based on a meta-analysis of 24 randomized controlled trials in LMIC, smoking abstinence at 6 months follow-up ( $P_{\text{control}}$ ) for usual care averages 10% (range, 8% to 14%). Assuming withdrawal from trial follow-up or loss to follow-up to be 5%, our sample of 25 PLWH per cluster per period has power of 87% to detect at least 10% increase (main effect,  $\Delta = (P_{\text{implementation}} - P_{\text{control}})$ ) in the primary endpoint at six months with the assumption that the event rate for those in control phase is 10% and two-sided alpha at intra-cluster correlation of 0.02.

[figure not shown]

Fig 5. Power to detect primary endpoint, main effect versus standard of care (SOC)

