As analysis of secondary outcomes at 6 months, 30-day point prevalence abstinence will be compared between the implementation and the control groups in a similar model to the one used in the analysis of the primary outcome. Longitudinal differences in the Stages of Change Algorithm between the implementation and the control groups will be compared using random-mixed effect regression. Analysis will be conducted to assess factors associated with completion of varenicline regimen using generalized estimating equation model for binary repeated measures.

## Statistical analysis for Study Objective 2

The CFIR will be used to guide qualitative interviews and activity log coding analysis. The CFIR-ERIC Matching Tool, which provides a menu of 39 constructs across five domains (Intervention Characteristics, Inner Setting, Outer Setting, Characteristics of Individuals, and Process), will be used to generate a list of potential strategies to address implementation barriers.

Qualitative data analysis. The CFIR will provide the structure for the initial codebook to guide qualitative data and activity log data using a descriptive content coding approach. The coding approach will be both deductive (codes derived from CFIR constructs) and inductive (codes derived from the data). During the coding and rating phases of analysis, the analysts will be blinded to the implementation effectiveness. Data will be independently coded by a revolving team of two analysts. Codes will be compared, and differences will be resolved by consensus discussion.

Quantification of qualitative data. We will quantify qualitative data and activity log data by having two analysts independently assign ratings for each code to reflect its positive or negative impact on implementation. Ratings will range from -2 to +2 with 0 to reflect a neutral or mixed influence of the code. For each facility, data will be consolidated, and two analysts will independently rate each code across all the interviews to obtain a facility rating for each time period. This process will be repeated for the two rounds of interviews and monthly for activity logs.

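### The protocol fixes its secondary outcomes twice with no member in common, so hypotheses ii to vi have no stated analysis and two of the listed outcomes have no questionnaire item behind them

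*Protocol*

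**What the plan says.** The protocol gives its efficacy aims in four places.

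- **Hypothesis (under Rationale).** Six directional statements, i to vi. The first is "Increase the proportion of smokers able to quit smoking". The other five concern quit attempts, length of abstinence ("Increase the length of abstinence in failed quit attempts"), cigarettes per day, and days of combustible use in two windows, ending with "Decrease the number of days of using combustible products within the past three months in people exposed to the intervention".
- **Clinical Outcomes.** One primary outcome is named: "Primary Outcome: The clinical effectiveness endpoint at six months is the 7-day point prevalence abstinence from combustible tobacco products". The Secondary Outcomes list follows: quit attempts, length of quitting in each attempt, current cigarette consumption, plus this item: "Number of days of using combustible tobacco products for at least 24 hours within the past month and the last 3 months".
- **Statistical Analysis for Study Objective 1.** After the primary model, the section turns to secondary outcomes: "As analysis of secondary outcomes at 6 months, 30-day point prevalence abstinence will be compared between the implementation and the control groups". It then compares Stages of Change over time between the groups. It closes with predictors of completing varenicline, which is not a comparison of the two phases.
- **Estimating process and outcome measures.** Item 4 says that the follow-up questionnaire measures 30-day as well as 7-day abstinence. Item 5 provides for the Stages of Change Algorithm at baseline and follow-up.

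**The concern.** A protocol may leave the detail of secondary models to a statistical analysis plan. This one has gone further and fixed the secondary set, in two sections that disagree completely. Any later plan that follows the outcome list departs from the analysis section, and the reverse.

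Two things are at stake. First, five of the six things the trial says BSMART will achieve have no analysis attached. Second, the text supports two different sets of secondary results, so which set is reported as the planned one could be settled after the data are seen. A separate, practical risk is that an outcome is listed and hypothesised but not collected in a form that yields it. That cannot be repaired once the visits have passed.

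**Working it through.** **What the power statement covers.** This check only establishes how many endpoints the sample size rests on.

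- Inputs from Study Design and Power and Sample size: 15 facilities, 25 participants per facility per period, 5% loss, intra-cluster correlation 0.02, 10% against 20%, two-sided. The alpha level is not printed; 0.05 is assumed.
- Per phase: 15 × 25 = 375, and 375 × 0.95 = 356.25, or 23.75 per facility.
- Design effect: 1 + (23.75 − 1) × 0.02 = 1.455. Effective n: 356.25 / 1.455 = 244.8.
- Standard error under the null: √(2 × 0.15 × 0.85 / 244.8) = 0.0323. Under the alternative: √((0.09 + 0.16) / 244.8) = 0.0320.
- z = (0.10 − 1.96 × 0.0323) / 0.0320 = 1.15, giving power 87.5%. With 25 in the design effect the result is 86.9%.

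The stated 87% is reproduced for one endpoint and one test. The formula ignores calendar time, so this is no judgement on whether the power is adequate for the stepped design.

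**The outcomes side by side.**

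| Outcome | Hypothesis | Secondary Outcomes list | Compared between phases in the Objective 1 analysis | Follow-up form |
|---|---|---|---|---|
| Quit attempts | ii | yes | no | B4, questions 5 and 6 |
| Length of abstinence | iii | yes | no | B4, question 7, most recent attempt only |
| Cigarettes smoked | iv | yes | no | B4, question 3 |
| Days of use, past month | v | yes | no | none |
| Days of use, past 3 months | vi | yes | no | none |
| 30-day point prevalence abstinence | not named | no | yes | B4, question 1 |
| Stages of Change | not named | no | yes | B5 |

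Counting the rows: five variables are listed and two are compared between phases, with none in common. Hypotheses without a stated analysis: 5 of 6. Listed variables with no follow-up item: 2 of 5.

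**Whether the form can supply days of use.** Question 4 of Appendix B4 asks on how many days of the week the participant smokes, with answers from 7 down to 1. Suppose a participant smoked daily and stopped exactly 7 days before the visit. Days of use in the past 30 are 30 − 7 = 23. Question 1 records smoking in the past 30 days, question 2 records none in the past 7, and question 4 offers no zero. Nothing on the form returns 23, and nothing covers a 3-month window.

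**Length of abstinence** is collected, but its definition shifts: failed attempts in the hypothesis, each attempt in the outcome list, the longest period since the last evaluation in item 4 of the measures, and the most recent attempt, in four categories, on the form.

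**The case against.** The strongest reply is that nothing here reaches the trial's main conclusion. That stands. The Rationale ties effectiveness to a single endpoint: "Effectiveness is defined as a 7-day biochemically verified point prevalence abstinence from combustible tobacco products at 6 months using CO Check". Clinical Outcomes labels it primary and the rest secondary, the sample size rests on it alone, and it has one primary analysis.

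A reader might therefore go too far and infer that the six hypotheses have no hierarchy, and that BSMART could be called effective on whichever of about eight tests (one primary, five listed, two analysed) turns out positive. The documents do not support this. Hypotheses ii to vi correspond to outcomes that the protocol itself calls secondary, and effectiveness is defined by the primary alone. A family-wise error rate over the eight would be the chance of some nominally significant result, not the error rate of the effectiveness claim. Nor does the phrase "interventions will have a substantial impact on primary endpoints compared to the control phase" show competing primaries: the same section then uses the singular, and no second primary endpoint is named anywhere.

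It can also be said that 30-day abstinence and Stages of Change are prespecified. As measures they are: both appear among the outcome measures, and Stages of Change is scheduled in Tables 2 and 3. They are absent only from the Secondary Outcomes list and the hypotheses. One could read 30-day abstinence into hypothesis i, which names no window, but that would not put it on the list. Nor is it the same outcome as days of use in the past month: one is yes or no, the other a count.

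Finally, multiplicity rules and secondary models are commonly left to a statistical analysis plan, which is not at hand. Their absence is not part of this point. A plan cannot, however, agree with two sections that disagree with each other.

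**Conclusion.** The contradiction is real and confined to the secondary outcomes. The listed and analysed sets do not overlap, five of six hypotheses have no stated analysis, and two of the five listed variables cannot be derived from the follow-up form as printed. The primary endpoint, its analysis and its power are untouched.

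The point is worth correcting because the correction is nearly free, lets the trial answer its own hypotheses, and closes an opening for selective reporting. The conclusion rests on reading the protocol text and its reproduced forms; it needs no assumption about alpha. If days of use are collected on an instrument not shown, the measurement part would fall away and the mismatch between the lists would remain.

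**What to change.** 1. Put one identical secondary outcome list in Clinical Outcomes and in Statistical Analysis for Study Objective 1, each outcome with its stated comparison. Add 30-day abstinence and stage of change to the outcome list. Add quit attempts, length of abstinence, cigarettes per day and days of use to the analysis section.
2. In the Hypothesis section, mark i as primary and ii to vi as secondary.
3. Either add follow-up items for days of combustible use in the past month and past 3 months, or redefine that outcome as what Appendix B4 collects. In the same edit, settle on one definition of length of abstinence that the form can supply.

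No ordered or adjusted testing of the secondary outcomes is required by this point. The cost is protocol wording and at most one or two questionnaire items. New items help only visits still to come, so they should be added before those visits take place.

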### Statistical analysis for study Objective 4.

Incremental cost-effectiveness ratio and net monetary benefit. The incremental cost-effectiveness ratio (ICER) is calculated as the ratio of the difference in mean costs and the difference in mean 7-day point prevalence abstinence at 6 months. The ICER (Figure 6) quantifies the additional cost associated with a

$$\text{ICER} = \frac{\text{Cost}_{\text{Implementation}} - \text{Cost}_{\text{Control}}}{\text{Effect}_{\text{Implementation}} - \text{Effect}_{\text{Control}}}$$

**Fig 6: ICER**

unit change in the 7-day point prevalence abstinence at 6 months, comparing between the implementation and control groups. Net benefit (NB) regression provides an appropriate approach to quantify the ICER using the incremental net monetary benefit (INMB) and produce a confidence interval around the ICER.

In equation 1 of Figure 7 we define NB as the difference between the monetized total effect measure (the product of lambda, the willingness to pay per unit of effect, and the total effect units available, e) and the associated costs. The NB regression model is specified in equation 2 of Figure 7 as the difference between effects and costs, estimated via a parametric regression framework where errors are represented by the final term in equation 2, epsilon. Alternative formulations of equation 2 include a generalized linear regression model that incorporates a skewed distribution of the NB. We will identify the initial value of lambda following a targeted literature review and consultations with onsite study collaborators. In equation 2 of Figure 5, the NMB, represented by the  $\beta$  coefficient on the indicator variable for receipt of intervention (i.e., 'Implementation'), will be estimated using the NB regression model.

$$NB_{ij} = (\lambda - e_{ij}) - c_{ij} \dots \dots \dots (1)$$

$$NB_{ij} = \beta_0 + \beta_1 \times \text{implementation}_{ij} + \epsilon_{ij} \dots \dots \dots (2)$$

**Fig 7: Net Benefit**

Sensitivity Analysis: Uncertainty in the estimated incremental cost-effectiveness ratios (ICERs) will be represented using the cost-effectiveness acceptability curve. Parameter uncertainty in the choice of the economically preferred intervention (between control and implementation periods) will be represented by the conditional net benefit (cNB) curve. The cNB curve plots the cNB (i.e., the net benefit value given a particular value of the parameter of interest) across centiles of the distribution of the parameter of interest. Sensitivity analyses will include probabilistic one-way sensitivity analyses (POSA) of cost input parameters (e.g., drug costs). Uncertainty in cost inputs will be investigated via designed simulations that use alternative values of cost inputs as determined by draws from assigned distributions (e.g. gamma, lognormal), with distributional parameters estimated from data collected from ongoing studies in Botswana. The POSA varies a specific input parameter value across its full distribution while accounting for concurrent variation in all other parameter values using Monte Carlo simulation, The cNB curve developed from the planned POSA will allow decision makers to identify the impact of the value taken by a specific cost parameter on the value of the BSMAART intervention.

## Study timeline

BSMART is a 5-year study:

Year 1: Protocol approvals will be obtained. A stakeholder meeting will be initiated. Standard operating procedures and manuals will be developed. Training of implementation leaders, lay health worker (LHW) case managers, nurse prescriber-dispensers (NPD), research assistants, and other facility healthcare workers will be conducted. Focus group discussions and Semi-Structured Interviews will be held with study participants, LHW case managers and NPDs.

Year 2: Screening and enrollment will be 12 months. In the trial, each participant will be followed for 24 weeks. Trial quality and compliance will be heavily monitored within the context of intervention implementation, data collection, and data quality.

Year 3: Qualitative studies on trial adoption and implementation delivery will be conducted. Participants' follow-up will be concluded.

Year 4: Analysis of trial primary endpoints and subgroup analysis will be conducted.

Year 5: Preliminary cost evaluation of the intervention will be conducted to focus on integration of the interventions into the HIV care system. Analysis for maintenance at the patient level i.e. durability of the intervention and at the facility level i.e. continuation with the interventions after the withdrawal of the interventions will be conducted. A final stakeholder meeting to focus on dissemination will be held.

|                                                                      | Year 1 |    |    |    | Year 2 |    |    |    | Year 3 |    |    |    | Year 4 |    |    |    | Year 5 |    |    |    |
|----------------------------------------------------------------------|--------|----|----|----|--------|----|----|----|--------|----|----|----|--------|----|----|----|--------|----|----|----|
| Timeline for Major Activities                                        | Q1     | Q2 | Q3 | Q4 |
| Data Management system in place                                      | X      |    |    |    |        |    |    |    |        |    |    |    |        |    |    |    |        |    |    |    |
| Stakeholder Advisory Group & Practitioner Engagement Group Meetings  |        | X  | X  | X  | X      | X  | X  | X  | X      | X  | X  | X  | X      | X  | X  | X  | X      | X  | X  | X  |
| Protocols, surveys, approval                                         |        | X  |    |    |        |    |    |    |        |    |    |    |        |    |    |    |        |    |    |    |
| Adaptation of intervention through qualitative FGs with CMs and NPDs |        | X  | X  |    |        |    |    |    |        |    |    |    |        |    |    |    |        |    |    |    |
| U01 network meeting with NIH/NCI                                     |        |    | X  |    |        |    | X  |    |        |    | X  |    |        |    | X  |    |        |    | X  |    |
| Training of LHW CMs and NPDs                                         |        |    | X  | X  | X      |    | X  | X  | X      |    | X  | X  | X      |    |    |    |        |    |    |    |
| Recruitment and enrollment                                           |        |    |    | X  | X      | X  |    | X  | X      | X  |    | X  | X      | X  |    |    |        |    |    |    |
| Follow-up to 24-weeks (post intervention)                            |        |    |    |    | X      | X  | X  | X  | X      | X  | X  | X  | X      | X  | X  | X  | X      | X  | X  | X  |
| Interviews on feasibility and acceptability                          |        | X  | X  | X  | X      | X  | X  | X  | X      | X  | X  | X  | X      | X  | X  | X  | X      | X  | X  | X  |
| Analysis of trial outcomes                                           |        |    |    |    |        |    |    | X  | X      |    |    | X  | X      | X  | X  |    | X      | X  | X  | X  |
| Analysis of qualitative implementation data                          |        |    |    |    |        |    |    |    |        |    |    |    |        | X  | X  | X  | X      | X  |    |    |
| Preliminary cost evaluation                                          |        |    |    |    |        |    |    | X  | X      |    |    | X  | X      |    |    | X  | X      | X  | X  |    |
| Analysis of durability and HIV data                                  |        |    |    |    |        |    |    |    |        |    |    |    |        |    |    |    | X      | X  | X  |    |

## Ethics and Protection of Human Subjects

### Risks to Human Subjects

All UMB research meets the requirements for the conduct of research using funds from the U.S. Government. We maintain Federal Wide Assurances (FWA) and with the NIH Office for Human Research Protections (OHRP)- approved institutional review boards (IRBs) in Botswana and the U.S. This protocol, the informed consent documents, study procedures, study documents, and any subsequent modifications will be reviewed and approved by all relevant IRBs responsible for the oversight of the study – the UMB IRB and the Health Research Development Committee (HRDC) of Botswana. All staff who will have contact with participants will receive training on the protection of human subjects in research prior to conducting any study activities and bi-annually thereafter. Key staff will also complete Good Clinical Practices training every three years.

### **1. Human Subjects Involvement, Characteristics, and Design**

The proposed research will involve human subjects as study participants. All procedures will be conducted according to the local standards of routine clinical care. Guided by the RE-AIM framework, our proposal will assess the Reach and Effectiveness of the BSMART interventions, its Adoption and Implementation, and how the BSMART interventions are Maintained over time and across outpatient HIV care facilities. In addition to the implementation trial, we will also conduct semi-structured interviews (SSIs) with study participants, and facility healthcare workers. SSIs conducted by the research team will be used to elicit perceptions, barriers, and stigma from participants at week 24. Focus group discussions (FGDs), which are ideal for identifying normative understandings following the generation of multiple perspectives, will be used with lay healthcare workers and nurse prescribers around the challenges of implementing the intervention and its integration with HIV care. Participants have the right to withdraw from the study procedures, semi-structured interviews, and focus group discussions at any time.

UMB's HIV treatment and care projects in Botswana:

UMB, the Prime Applicant for this study, and the Botswana University of Maryland Medicine Health Initiative (BUMMHI), a subrecipient for this study, currently collaborate on the Accelerating Botswana through the Last Mile to Epidemic Control (ABLE) project providing support for HIV care and treatment in 53 high-volume facilities across Botswana, including the 15 selected and 4 reserve sites proposed for this study, and will provide support through 2025, when the human subjects research at the facilities will be performed. The Botswana National AIDS and Health Promotion Agency (NAHPA) has confirmed the

investigators' access to these facilities to recruit participants and conduct the proposed study (see Letters of Support).

